#### Sample size

Based on the formula for calculating the sample size of a cohort study at one-side significance level: [22].$$N={\left[\frac{u_{\alpha}\sqrt{2\overline{p}\left(1-\overline{p}\right)+}{u}_{\beta}\sqrt{p_1\left(1-{p}_1\right)+{p}_2\left(1-{p}_2\right)}}{p_1-{p}_2}\right]}^2$$

According to the previous studies, the prevalence of precocious puberty was 4.85% (*P*_2_) and 8.43% (*P*_1_) of children aged 7–10 years with normal weight and overweight, respectively [12, 23]. A type I error (*α*) of 0.05, u_0.05_ = 1.96;, β = 0.10, u_0.10_ = 1.28; and a loss of follow up rate of 15%, a total of 4152 children will be required in each center. Finally, inverse-variance weighting (IVW) methods will be used to adjust the sample size.

Based on the SNP gene differences between different groups reported in the literature, Quanto 1.2.4 software (John Morrison, W. James Gauderman 2009, University of Southern California) was used to estimate sample sizes for each group. According to the previous pre-experimental results of obesity study showed that the allele frequency was 0.30 and the minimum allele frequency (MAF) was 0.10 using Additive Genetic Model (ADD), the type I error (α) of 0.05, the actual Power is 0.80, we need average of 800 participants per group and 3200 cases for four groups. Cases among four groups will be controlled by sex and age.

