Previous studies on the relationship between obesity and precocious puberty have mostly been cross-sectional studies, with few studies on pleiotropic genes of obesity and puberty. To explore the relationship between obesity and puberty development, this prospective cohort study will investigate the genetic, parental, social and family environment, lifestyle, and other determinants of puberty development. This protocol describes an overview of the design and methods of this cohort study, which is funded by the National Natural Science Foundation of China (grant number 81872637). The study objectives are as follows: I) analyzing the incidence of precocious puberty in the general population in China, examining the direct effect of childhood obesity on precocious puberty; II) exploring the relationship between prepuberty obesity and its risk genes and precocious puberty; III) determining the relationship between prepuberty obesity and its risk genes and hormone levels among children with precocious puberty; and IV) analyzing the interaction effect between genes and environmental factors on precocious puberty.

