## Methods

### Study design, setting, and participants

#### Study design and sampling

This study is a prospective multi-center cohort study sponsored by the Shanghai Children’s Medical Center affiliated to the School of Medicine, Shanghai Jiao Tong University and performed in three cities in southern, central, and northern China, namely, Zhongshan, Guangdong Province, Qufu, Shandong Province, and Dalian, Liaoning Province. According to socioeconomic level and geographical distribution, the districts of Zhongshan, Qufu, and Dalian are stratified into urban districts in the central area and suburban districts in suburban areas. Using a stratified cluster random sampling method, districts and schools will be selected according to geographical location and school size by a random number generator. Grade 1, 2, and 3 children (6 to 10 years old) from primary schools will be included in this study. However, participants with overweight or obesity with a history of hormone treatment in the past 6 months as reported by parents in the questionnaire will be excluded.

We will carry out a nested case-control study, which will be nested in this cohort study. Participants in case-control study will be enrolled in four groups: children with normal weight and normal puberty, with normal weight and precocious puberty, with overweight/obesity and normal puberty, and with overweight/obesity and precocious puberty. And they will be measured body composition, collected venous blood, and stool at baseline, and collected urine samples at baseline and follow-up periods.

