#### Sexual development assessment

The primary outcome is the difference in incidence of precocious puberty between normal-weight and obese children.

Secondary sexual characteristics assessment for boys and girls will be conducted by male and female professional pediatric endocrinologists or pediatric care physicians separately in different rooms to protect the children’s privacy. Breast development will be evaluated by visual inspection and palpation. Girls with overweight or obesity will be subjected to breast ultrasound to evaluate their nodules. In boys, testicular volume (TV) will be determined by palpation and an orchidometer. According to Marshall and Tanner [26, 27], breast and pubic hair development are divided into 5 stages (stages I to V). Precocious puberty will be diagnosed according to the Tanner stage: onset of breast development stage II (B_2_) or pubic hair development stage II (PH_2_) or above before 8 years or menarche before 10 years of age in girls, and PH_2_ or testicular enlargement (TV ≥ 4 ml) before 9 years of age in boys [28–30].

The presence of early puberty will be defined as children reaching a certain stage of puberty earlier than the median age of that stage [31]. According to previous studies, the median age of puberty onset (girls: breast or pubic hair development; boys: pubic hair or testicular volume development) of Chinese adolescents will be referenced [32, 33], and the onset of menarche before 12 years of age in girls and of voice breaking before 13 years of age in boys will also be defined as early puberty [34].

We separately evaluated the tanner stage for each breast among obese girls by using portable ultrasound (US), and chose the larger one as evaluation result. Tanner II by US is characterized as the presence of a hyperechoic retro-areolar nodule with a central star-shaped or linear hypoechoic area, this stage is assumed to mark the start of breast development [35].

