**Age (years)**			
6 ≤ age<8	2365 (59.23)	2821 (60.93)	5186 (60.14)
8 ≤ age<11	1628 (40.77)	1809 (39.07)	3437 (39.86)

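### The per-centre power is planned on prevalences at ages 7–10, but the primary outcome is incidence, so the stated 90% is not supported for that outcome

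*Protocol article*

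**What the plan says.** All references are to the Protocol article.

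- **Planning inputs (Sample size).** The section uses a "formula for calculating the sample size of a cohort study at one-side significance level". Its rates are described thus: "the prevalence of precocious puberty was 4.85% (*P*_2_) and 8.43% (*P*_1_) of children aged 7–10 years", the lower rate for normal-weight and the higher for overweight children. The constants are "u_0.05_ = 1.96;, β = 0.10, u_0.10_ = 1.28". It allows 15% loss to follow-up and asks for 4152 children in each centre.
- **Primary outcome (Sexual development assessment).** "The primary outcome is the difference in incidence of precocious puberty between normal-weight and obese children". Objective I at the end of the Background also names incidence: "analyzing the incidence of precocious puberty in the general population in China".
- **Who enters (Study design and sampling).** "Grade 1, 2, and 3 children (6 to 10 years old) from primary schools will be included in this study". The only stated exclusion concerns overweight or obese children with recent hormone treatment. Children already precocious at baseline are neither excluded nor explicitly kept in the incidence denominator.
- **Case definition (Sexual development assessment).** Girls: breast or pubic hair stage II before 8 years, or menarche before 10. Boys: pubic hair stage II or testicular volume of at least 4 ml before 9 years.
- **Follow-up.** The Study procedure schedules visits one and two years after baseline. The Abstract promises at least three years, and the Data analysis section refers to three years' follow-up.
- **Enrolled so far (Table 3, Qufu and Zhongshan).** Of 8623 children, 3437 (39.86%) were aged 8 to under 11 at baseline, including 1628 of 3993 girls (40.77%).

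**The concern.** A cohort calculation needs the probability of the outcome event over follow-up among children who can still have it. A prevalence is the proportion who have the condition in a given age band, and the section does nothing to convert one into the other. The 15% allowance for loss to follow-up shows that the rates were meant to stand for something observed during follow-up, so the calculation cannot simply be read as a plan for a baseline prevalence comparison.

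The case definition makes the difference material. A girl who enters at 8 or older can become a new case only through menarche before 10. A boy who enters at 9 or older cannot become one at all. Yet such children count in full towards the 4152.

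What is at stake is the reading of a null result. A centre-level comparison of incidence that finds nothing could be presented as coming from a study with 90% power, when that figure was derived for a different quantity.

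**Working it through.** **1. The plan's own figure.** The printed formula with p₁ = 0.0843, p₂ = 0.0485, p̄ = 0.0664, u_α = 1.96 and u_β = 1.28:

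N = [(1.96 × 0.3521 + 1.28 × 0.3512) / 0.0358]² ≈ 1,014 per group.

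Dividing by 0.85 gives 1,193 per group, or 2,386 for two equal groups. This does not reproduce 4152. That gap, and the use of 1.96 with a formula called one-sided, are separate matters. Here 4152 is taken as given.

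**2. Numbers followed per centre.** 4152 × 0.85 = 3,529. Table 3 has 21.79% overweight or obese and 62.57% normal weight; thin children are in neither group.

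- Overweight/obese: 3,529 × 0.2179 = 769
- Normal weight: 3,529 × 0.6257 = 2,208

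**3. Share at risk at entry.** Table 3 splits age at 8 only. Girls under 8 plus all boys: (2365 + 4630) / 8623 = 81.1%. Apart from the route through menarche before 10, this is an upper bound, because it keeps boys aged 9 or over and removes no baseline case. The numbers become 769 × 0.811 = 624 and 2,208 × 0.811 = 1,791. This assumes that the weight split is the same among those at risk; Table 3 does not cross-tabulate age with weight.

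**4. Power.** Two-sided, z = 1.96:

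Power = Φ[(p₁ − p₂ − 1.96·s₀) / s₁], where

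- s₀ = √[p̄(1 − p̄)(1/n₁ + 1/n₂)], with p̄ the weighted mean rate
- s₁ = √[p₁(1 − p₁)/n₁ + p₂(1 − p₂)/n₂]

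Printed rates, all children: (0.0358 − 1.96 × 0.00977) / 0.01101 = 1.51, so power is 93.5%.

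Printed rates, 81.1% at risk: (0.0358 − 1.96 × 0.01084) / 0.01223 = 1.19, so power is 88.3%.

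The article gives no incidence. As an assumption, both rates are scaled by 0.75 and 0.5 with their ratio (1.74) kept:

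| Rates (overweight/obese v normal) | At risk | n per centre | Power per centre | Power, three centres pooled |
|---|---|---|---|---|
| 8.43% v 4.85% (printed) | all | 769 v 2,208 | 93% | >99% |
| 8.43% v 4.85% (printed) | 81.1% | 624 v 1,791 | 88% | >99% |
| 6.32% v 3.64% (×0.75) | 81.1% | 624 v 1,791 | 78% | 99.6% |
| 4.22% v 2.43% (×0.5) | 81.1% | 624 v 1,791 | 62% | 96% |

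The pooled column uses three times the per-centre numbers. No figure allows for clustering by school.

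**The case against.** **Pooling removes most of the numerical harm.** The article describes one multicentre cohort and nowhere says that the primary outcome is tested centre by centre. Pooled power stays above 95% in every row of the table. This stands, and it limits the point. But the section sets its requirement for each centre, so the per-centre power is the claim being made.

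**Lower rates are assumed, not shown.** The multipliers 0.75 and 0.5 come from nowhere in the article. If children outside the age window can no longer become cases, removing them could leave a higher rate in the remainder, so cutting both the denominator and the rate may count one effect twice. This also stands. The article settles neither the size nor the direction of the change in rate. Even the 88% applies the printed rates to the children at risk.

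**Baseline cases may be meant to count.** Precocious puberty is defined by onset before a fixed age, so the proportion affected by that age could be treated as a cumulative incidence, with prevalence a fair proxy. That reading is possible, but the article does not adopt it, and the denominator would still have to be stated.

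**Stronger readings that the article does not support.**

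- A reader might restrict the at-risk group to children under 8 (5186 / 8623 = 60.1%), which at half the printed rates gives about 51% per centre. That drops boys aged 8 to under 9, who can still become cases. Even then pooled power is about 90%.
- A reader might also stress that the rates start at age 7 and enrolment at 6. The ranges overlap heavily and six-year-olds reach 7 by the first visit, so this gap is minor.

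**Conclusion.** The concern holds as a mismatch between the planning quantity and the primary outcome. The β = 0.10 target rests on prevalences, the primary outcome is incidence, and nothing links the two. If incidence means new cases, the 90% per centre is unsupported. Allowing only for children past the age limit takes per-centre power from about 93% to about 88%; at assumed incidences of 75% or 50% of the printed rates it is about 78% or 62%.

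These figures rest on the Table 3 weight split holding in every centre and among those at risk, 15% loss, overweight and obese children combined, a constant rate ratio and no clustering.

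A reader might infer that the study is underpowered. The article does not show that: pooled power in the two reduced-rate cases is about 99.6% and 96%, and the true incidence is unknown.

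**What to change.** 1. In the Sexual development assessment section, define the primary incidence: which children are at risk at baseline, over what follow-up period, and whether cases present at baseline count. The one- and two-year visits and the three-year follow-up mentioned elsewhere should be reconciled in that definition.
2. In the Sample size section, label 4.85% and 8.43% as prevalences at 7–10 years.
3. Restate power for the incidence outcome over a stated range of assumed incidences, using the number at risk rather than the number enrolled, per centre and for the three centres pooled. Incidences fixed in advance are preferable to the first-year results from Zhongshan and Qufu, since power computed from the study's own outcomes is close to post hoc power.

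Enrolment does not change. The cost is a recalculation and a less favourable per-centre power statement.

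### The 4152 children per centre cannot be derived from the printed formula and inputs, which give 2386, and the one-sided label contradicts the quantile 1.96

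*Protocol article*

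**What the plan says.** The Sample size section introduces its calculation as follows: "Based on the formula for calculating the sample size of a cohort study at one-side significance level". The formula is the usual equal-group comparison of two proportions. Its inputs are a precocious puberty prevalence of 4.85% in normal-weight and 8.43% in overweight children, a type I error of 0.05 with u = 1.96, and "β = 0.10, u_0.10_ = 1.28". The result follows at once: "and a loss of follow up rate of 15%, a total of 4152 children will be required in each center". The section then says that inverse-variance weighting will adjust the sample size, without giving a factor. It states no allocation ratio, continuity correction, stratum multiplier or design effect, although the Study design section describes stratified cluster random sampling of districts and schools.

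The Sexual development assessment section defines the endpoint: "The primary outcome is the difference in incidence of precocious puberty between normal-weight and obese children". The Data analysis section sets significance at p < 0.05 and does not say whether tests are one- or two-sided.

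**The concern.** When an article prints the formula, every input and the answer, the answer should follow. Here it does not. The sidedness is also stated in two incompatible ways: one-sided 0.05 corresponds to 1.645, while 1.96 is two-sided 0.05 or one-sided 0.025. The type I error behind the main planning number is therefore uncertain by a factor of two, and the analysis section does not settle it.

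A reader cannot tell what 4152 was built to deliver: which error rate, how many groups or strata, and whether any of the excess was meant to cover clustering by school. In addition, the rates used for planning are for normal-weight and overweight children, while the primary outcome compares normal-weight and obese children.

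**Working it through.** **Inputs** (Sample size section): P1 = 0.0843, P2 = 0.0485, difference 0.0358, mean rate (0.0843 + 0.0485)/2 = 0.0664, u = 1.96 and 1.28, loss 15%.

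**1. The printed calculation.** N per group = {[u_α √(2p̄(1−p̄)) + u_β √(P1(1−P1) + P2(1−P2))] / (P1−P2)}².

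- √(2 × 0.0664 × 0.9336) = 0.35211
- √(0.0843 × 0.9157 + 0.0485 × 0.9515) = 0.35120
- (1.96 × 0.35211 + 1.28 × 0.35120)/0.0358 = 1.13967/0.0358 = 31.834
- 31.834² = 1013.4, so 1014 per group and 2028 in total
- 2028/0.85 = 2386 (or 2028 × 1.15 = 2332)

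The stated 4152 is 4152/2386 = 1.74 times this. As typeset, a plus sign sits inside the first radical. Nesting the second root there is not a valid formula, and it gives about 4045, still not 4152.

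**2. Taking the one-sided label at its word.** With u_α = 1.645: (1.645 × 0.35211 + 1.28 × 0.35120)/0.0358 = 28.736. Squared, this is 825.8, so 826 per group, 1652 in total, and 1652/0.85 = 1944. The gap widens to 4152/1944 = 2.14.

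**3. A route that does reach 4152.** Use 1.645 and the less rounded 1.2816, so that n = 826.7. Then apply the standard continuity correction, n′ = (n/4)[1 + √(1 + 4/(n × 0.0358))]².

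- n′ = (826.7/4)(1 + √1.13516)² = 881.7, so 882 per group
- 882/0.85 = 1037.6, so 1038
- 1038 × 4 = 4152

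With the printed 1.28 the same route gives 881, then 1037, then 4148, so the exact match also needs the unrounded quantile. With 1.96 and 1.28 it gives 1069, then 1258, then 5032. The route therefore works only if 1.96 was not used.

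**4. What 4152 delivers.** Table 3, pooled over the two centres surveyed, shows 62.57% normal weight, 21.79% overweight or obese, and 15.64% thin, who belong to neither comparison group. Completers are 0.85 × 4152 = 3529, of whom 0.2179 × 3529 = 769 are overweight or obese and 0.6257 × 3529 = 2208 are normal weight.

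- Pooled rate = (769 × 0.0843 + 2208 × 0.0485)/2977 = 0.05775
- SE under no difference = √(0.05775 × 0.94225 × (1/769 + 1/2208)) = 0.009767
- SE under the planned rates = √(0.0843 × 0.9157/769 + 0.0485 × 0.9515/2208) = 0.011013
- Two-sided power: Φ((0.0358 − 1.96 × 0.009767)/0.011013) = Φ(1.512) = 93.5%
- One-sided power: Φ((0.0358 − 1.645 × 0.009767)/0.011013) = Φ(1.792) = 96.3%

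These figures ignore clustering. Dividing both groups by a design effect of 1.16 brings two-sided power to 90.0%. The article gives no intracluster correlation, so the actual design effect is unknown.

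**The case against.** The best defence is the route in step 3. It keeps the stated rates, the one-sided label, α = 0.05, β = 0.10 and the 15% loss, and it lands on 4152. Four cells could be two weight groups by two sexes, since the outcome is defined by sex, or by urban and suburban stratum. A condensed article may leave out a correction and a multiplier. On that reading 4152 is a real one-sided calculation and 1.96 is the misprint. This stands as a possibility. It is not proof: the correction and the factor of four are stated nowhere, and the printed 1.96 contradicts it. It also leaves the printed text wrong, because the article does not merely omit steps: it gives a formula and inputs that disagree with its result.

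Two stronger readings are tempting, and the documents support neither.

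- A reader might infer that the one-sided label should be deleted and the requirement restated, either as 2386 or, with Table 3's mix and thin children added, as 3580 (2567 completers/0.8436/0.85). The text does not show whether the label or the quantile is the slip. Table 3 was observed after planning and in two of three centres, and neither figure includes a design effect.
- A reader might infer that the study is underpowered. On the stated rates 4152 exceeds 1944, 2386 and 3580, and its power is above 90% under either sidedness before clustering.

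**Conclusion.** The point holds as an error of statement. The printed formula and inputs give 2386 per centre, not 4152, and one-sided 0.05 is incompatible with 1.96. Both conclusions rest on the Sample size section alone and on equal groups, which the printed formula assumes. The sidedness conflict is a separate error, because resolving it towards one-sided moves the result further from 4152.

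The figure is not derivable; it is not shown to be inadequate. The 93.5% and 96.3% power figures assume the planned rates, the Table 3 mix for overweight and obesity combined, 15% loss and independent children. The two-sided margin is thin, since a design effect above about 1.16 takes power below 90%. That is a reason to state what the excess covers, and it does not show a shortfall.

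The overweight-versus-obese difference is secondary. It explains none of the numerical gap, and the planning text may mean overweight to include obesity.

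**What to change.** - Reconcile the sidedness with its quantile, and state the same sidedness for the analysis of the primary outcome.
- Restate the calculation so that the formula, quantiles, any continuity correction, number of groups or strata, loss step and any design effect for school sampling actually yield 4152. If they do not, correct the number.
- Report the power that 4152 per centre gives for the intended contrast with unequal groups and thin children left out, and say how far it tolerates clustering.
- Name the same contrast in the Sample size and Sexual development assessment sections. Which contrast is for the authors to choose.

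The cost is wording and recalculation. Enrolment need not change: Table 3 already shows 8623 children in two centres, against 2 × 4152 = 8304.

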#### Biospecimen collection and laboratory examination

Children with overweight or obesity and some of the participants with normal weight (matched for sex and age) will be recruited to collect venous blood at baseline; urine samples will be collected at baseline and 1-year follow-up. A total of 2 ml and 1 ml venous blood will be collected in coagulation and anticoagulation collection tubes, respectively. These participants will receive a vacuum stool collection tube and 15-ml urine tube 1 day before physical inspection, and they will be asked to collect stool and urine samples in the morning and take them to the researchers at school on the physical inspection day. All of the biological sample will be transferred with an ice bag to a local collaborating hospital within 2 hours after collection. Blood samples in coagulation collection tubes will be centrifuged to extract serum. Then, all biospecimens will be transferred with dry ice to the Biobank of Shanghai Children’s Medical Center and stored at − 80 °C.

Part of the serum sample will be used to test follicle-stimulating hormone (FSH), luteinizing hormone (LH), and estrogens (E2) in girls and testosterone (T) in boys; the residual serum will be used to test leptin, kisspeptin, and ghrelin levels. A whole-blood sample will be used to analyze the pleiotropic genes of precocious puberty and obesity.

Simultaneous quantification of 64 steroids, including EED in pediatric plasma and urine by LC–MS/MS. Using the SNaPshot technology of ultra-high throughput SNP typing to detect genetic markers, thousands of SNP loci can be detected in each reaction. ABI3730XL sequencer was used for simultaneous detection of several samples.

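### The nested genetic study is sized at an average of 800 children per group for 0.80 power, but on the plan's own figures the cohort supplies only about 229 and 378 children for the two precocious-puberty groups

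*Protocol article*

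**What the plan says.** Under Study design and sampling, the protocol article states: "We will carry out a nested case-control study, which will be nested in this cohort study". The four groups cross weight status (normal, or overweight/obese) with puberty status (normal or precocious).

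Under Sample size, the genetic study is sized with Quanto. The inputs are described as "Based on the SNP gene differences between different groups reported in the literature", with "the type I error (α) of 0.05, the actual Power is 0.80". The result is "we need average of 800 participants per group and 3200 cases for four groups". The odds ratio, the sidedness of the test and the contrast being powered are not given.

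The same section sizes the cohort at 4152 children per centre, in three centres, from these rates: "the prevalence of precocious puberty was 4.85% (*P*_2_) and 8.43% (*P*_1_) of children aged 7–10 years with normal weight and overweight, respectively".

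Table 3 gives the baseline weight split for the two cities enrolled so far: 62.57% normal weight and 21.79% overweight or obese among 8623 children.

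**The concern.** A nested study cannot contain more cases than its parent cohort. The plan sizes the cohort from low precocious-puberty rates, then sizes the genetic study as if each precocious-puberty group could reach about 800 children. It does not check one calculation against the other.

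Objectives II to IV in the Background use risk genes or gene-environment interaction, and the Data analysis section plans a trend test of the genetic risk score across these four groups. Objective III is confined to children with precocious puberty: about 607 on the plan's figures, not the 1600 that two groups of 800 imply. If 0.80 stands as printed, a null genetic result involving the precocious-puberty groups could be read as coming from an 80%-powered comparison when it did not.

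**Working it through.** **The plan's own figure.** 4 x 800 = 3200 is correct. The 800 itself cannot be reproduced, because the odds ratio entered in Quanto is not stated. The check is therefore whether the cohort can supply the groups.

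**Inputs.** Cohort: 3 x 4152 = 12,456 (Sample size; three cities under Study design). Precocious-puberty rates: 8.43% and 4.85% (Sample size). Weight shares: 21.79% and 62.57% (Table 3). Loss to follow-up: 15% (Sample size).

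**Expected cases** = cohort x weight share x rate.
- Overweight/obese: 12,456 x 0.2179 x 0.0843 = 229 (29% of 800).
- Normal weight: 12,456 x 0.6257 x 0.0485 = 378 (47% of 800).
- Together: 229 + 378 = 607.

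**Expected normal-puberty children.** Overweight/obese: 12,456 x 0.2179 x (1 - 0.0843) = 2485. Normal weight: 12,456 x 0.6257 x (1 - 0.0485) = 7416. These two groups can easily supply 800 each or more.

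**What 800 cases would require.**
- Overweight/obese: a cohort of 800 / (0.2179 x 0.0843) = about 43,550, or a rate of 800 / (12,456 x 0.2179) = 29.5% in the planned cohort.
- Normal weight: a cohort of 800 / (0.6257 x 0.0485) = about 26,360, or a rate of 800 / (12,456 x 0.6257) = 10.3%.

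**Conditional power.** Assume that 0.80 refers to 800 v 800 at two-sided 0.05. For a fixed allele effect, the standard error scales with sqrt(1/n1 + 1/n2). Write m = n1 x n2 / (n1 + n2), so that 800 v 800 gives m = 400. Then

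power = Φ( (1.96 + 0.84) x sqrt(m / 400) - 1.96 ).

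In this approximation the unstated odds ratio and the allele frequency cancel out.

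| Scenario | Overweight/obese cases v 800 | Normal-weight cases v 800 |
|---|---|---|
| 15% of cases lost | 194: m = 156, power 0.42 | 321: m = 229, power 0.56 |
| Plan's rates | 229: m = 178, power 0.46 | 378: m = 257, power 0.61 |
| Rates doubled (assumption) | 458: m = 291, power 0.67 | 756: m = 389, power 0.79 |

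Comparing the two precocious-puberty groups with each other at the plan's rates (229 v 378, m = 143) gives about 0.39.

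**Same total, unequal groups.** With all 607 cases and 3200 - 607 = 2593 normal-puberty children, m = 607 x 2593 / 3200 = 492 and power is about 0.87. Stratifying by weight changes little. With 1600 places per weight group, m = 229 x 1371 / 1600 + 378 x 1222 / 1600 = 196 + 289 = 485, again about 0.87. If 15% of cases are lost, 194 + 321 = 515 v 2685 gives m = 432 and about 0.83.

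**The case against.** **The text says an average of 800.** This stands. Unequal groups are compatible with an average, and 3200 in total is attainable. A reader might infer that the genetic study as a whole cannot be carried out, or that every genetic analysis loses its 0.80. The documents do not support that. A pooled precocious v normal-puberty contrast keeps its power, and a gene comparison between weight groups is not limited by the number of precocious cases. What does not survive is carrying a per-group size and its power over to groups well below that size; the plan states neither the unequal allocation nor its power.

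**The plan names no pairwise contrast.** This stands too. The Data analysis section lists a genetic risk score, a trend test over four groups, regression and Mendelian randomization. The 0.46 and 0.61 are therefore conditional illustrations, not the study's delivered power.

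**The rates are point prevalences, and follow-up will add cases.** This stands in part. About 60% of children were under 8 at baseline (Table 3), and overweight or obese children give blood then, so later cases among them would already have DNA. But doubling both rates still leaves 458 and 756. New cases are also limited by the definition: onset must precede 8 years in girls (or menarche 10 years) and 9 years in boys, and 40.77% of girls were already 8 or older at baseline.

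**The weight shares come from two of three cities.** This is true, but the third would have to differ implausibly to close the gap. The 8623 children enrolled so far would yield about 158 and 262 cases. Counting thin children as normal weight raises 378 only to 12,456 x 0.7821 x 0.0485 = 472.

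**Conclusion.** The point holds as a conflict between the group sizes and the cohort meant to supply them. On the plan's own rates, the precocious-puberty groups reach about 29% and 47% of 800. Neither reaches 800 even with doubled rates, though the normal-weight group comes close. The stated 0.80 therefore does not carry over to comparisons involving a precocious-puberty group. On the assumption that it refers to 800 v 800 at two-sided 0.05, those comparisons have about 0.46 and 0.61 against 800 controls, or about 0.67 and 0.79 with doubled rates.

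The case counts rest on the plan's prevalences, the full cohort of 12,456 and weight shares from two cities; the power figures are normal approximations. The total of 3200 is not in question, and neither is the primary outcome, the difference in incidence of precocious puberty by weight.

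**What to change.** In the Sample size section:

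1. Replace the 800 per group with the attainable sizes and a range: about 229 overweight or obese and 378 normal-weight precocious cases, up to about 458 and 756 if follow-up doubles the rates. Take all precocious cases and fill the remaining places up to 3200 with normal-puberty children within weight group.
2. State the contrast, the odds ratio and the sidedness to which 0.80 applies.
3. Restate power at the attainable sizes for every comparison that involves a precocious-puberty group, including the four-group trend test.

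Optionally, also report the weight-stratified precocious v normal-puberty contrast, which keeps about 0.87 (607 v 2593), or about 0.83 if 15% of cases are lost. Whether to make it the leading genetic comparison is a design choice for the sponsor; the defect does not require it.

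The cost is some rewording and a recalculation; the number genotyped stays at 3200. The drawbacks are unbalanced groups and a less favourable stated power for the four-group contrasts.
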